## Abstract

**Background:**

Hypertension is one of the key factors causing cardiovascular diseases which make up the most frequent cause of death in industrialised nations. However about 60% of hypertensive patients in Germany treated with antihypertensives do not reach the recommended target blood pressure. The involvement of patients in medical decision making fulfils not only an ethical imperative but, furthermore, has the potential of higher treatment success. One concept to enhance the active role of patients is shared decision making. Until now there exists little information on the effects of shared decision making trainings for general practitioners on patient participation *and* on lowering blood pressure in hypertensive patients.

**Methods/Design:**

In a cluster-randomised controlled trial 1800 patients receiving antihypertensives will be screened with 24 h ambulatory blood pressure monitoring in their general practitioners’ practices. Only patients who have not reached their blood pressure target (approximately 1200) will remain in the study (T1 – T3). General practitioners of the intervention group will take part in a shared decision making-training after baseline assessment (T0). General practitioners of the control group will treat their patients as usual. Primary endpoints are change of systolic blood pressure and change of patients’ perceived participation. Secondary endpoints are changes of diastolic blood pressure, knowledge, medical adherence and cardiovascular risk. Data analysis will be performed with mixed effects models.

**Discussion:**

The hypothesis underlying this study is that shared decision making, realised by a shared decision making training for general practitioners, activates patients, facilitates patients’ empowerment and contributes to a better hypertension control. This study is the first one that tests this hypothesis with a (cluster-) randomised trial and a large sample size.

**Trial registration:**

WHO International Clinical Trials: http://apps.who.int/trialsearch/Trial.aspx?TrialID=DRKS00000125

## Background

Hypertension is one of the key factors causing cardiovascular diseases [1] which make up the most frequent cause of death in industrialised nations [2]. In spite of the high individual and societal burden of high blood pressure and cardiovascular disease respectively, about 60% of hypertensive patients in Germany treated with antihypertensives do not reach a target blood pressure of systolic / diastolic ≤ 140/90 mmHg in clinical measurement [3]. At the same time, scientific development and socio-cultural changes have initiated a change in medical decision making from a rather paternalistic towards a more participatory style in which both physician and patient play an active role. In Germany, patients are entitled to get fully informed on chances and risks of equivalent treatments [4]. In hypertension therapy, there is a considerable number of treatment alternatives, and patients want to be informed about options and take part in their treatment decisions [5].

One key concept to enhance patients’ active participation in medical decisions is shared decision making (SDM). It is characterised as an interactive process between physician and patient, acting according to the principle of equipoise. Both parties share information with the aim to build a consensus about the preferred treatment and its realisation. One precondition to realise SDM is the existence of equivalent treatment options [6,7].

It must be assumed that patients with hypertension who do not reach target blood pressure despite antihypertensive medication are – at least in their majority – not able to put behaviour change and / or medical adherence into practice. In these cases, first of all, general practitioners (GP) should support patients to improve their health behaviour [8-10].

Evidence on SDM interventions showed positive effects of SDM on patients’ participation, satisfaction with their treatment, decisional conflict, knowledge about the disease, adherence, and partly clinical outcomes [11-17]. Nevertheless, study designs, intervention programmes and measurement instruments vary considerably, sample sizes are often small and results are inconsistent.

Within the research programme “The patient as partner in medical decision making”, funded from 2001 by the German Ministry of Health, an SDM training programme for clinicians has been developed [6] and evaluated in various studies [14,18].

Until now there exists little information on the effects of SDM trainings for GPs on patient participation *and* clinical outcomes [19]. This holds also for blood pressure level in antihypertensive treatment where only one study (non-randomised and with a comparably small sample size) has been conducted until now [17]. The aim of our study is therefore to implement and evaluate an SDM training programme for GPs within the context of hypertension treatment in primary care.

### Research objectives

Our study attempts to answer the following research questions: Does the SDM training programme for GPs

1) enhance patients’ perceived participation?

2) optimise the blood pressure values of patients?

3) enhance patients’ knowledge about hypertension?

4) improve patient adherence?

## Methods/Design

The Ethical Committee of the University Medical Centre Freiburg approved this study on 26 February 2009. A non-substantial protocol amendment was approved on 7 March 2012 by the Ethical Committee of the University Medical Centre Freiburg.

### Study design

The study will be conducted as a cluster-RCT with 40 GP practices in the Suedbaden region, Germany. Patients who receive an antihypertensive medication will be invited to take part in the study. After a baseline data assessment (T0), GPs will be randomised into intervention group (SDM training and dissemination of printed patient information on hypertension and antihypertensive treatment) and into control group (no training, treatment as usual). After the intervention, three follow-up data assessments are scheduled (T1, T2 and T3; cf. Figure 1).

**Figure 1 F1:**
[figure not shown]
Study protocol diagram.

### Study population

#### General practitioners

About 120 GP practices of a network of accredited general practitioners and academic GP practices associated with the Department of General Practice of the University Medical Centre Freiburg (Germany) will be informed about the study.

#### Patients

Each participating GP is asked to include 30 patients in the study who are currently treated for hypertension. These patients have to fulfil the following criteria.

Inclusion criteria: (1) Repeated prescription of antihypertensive medication, (2) at least 18 years old, (3) insured by a statutory health fund, (4) understanding of the German language.

Exclusion criteria: Dementia, mental handicap, or short life expectancy

#### Recruitment procedure

To assure a random sample of the patients in each GP practice, medical assistants of the practices (MA) will be instructed to invite every third consecutive patient fulfilling the inclusion criteria to take part in the study. For all patients fulfilling the inclusion criteria and willing to take part in the study, a baseline assessment is performed. This includes ambulatory blood pressure measurement (ABPM) to screen blood pressure control in all recruited patients, further clinical data and a patient questionnaire. Recruiting takes place over half a year.

After baseline ABPM, patients will be classified as ‘controlled’ treated if their blood pressure values are below the thresholds for hypertension measured by ABPM: mean values for 24 h ≤ 130/80 mmHg, ≤ 135/85 mmHg during the day, and ≤ 120/70 mmHg at night [1,20]. These patients with ‘controlled’ hypertension will be excluded from the study if none of the following comorbid disorders are diagnosed: diabetes mellitus, coronary heart disease / heart attack, stroke / transient ischaemic attack (TIA) or peripheral arterial occlusive disease (PAOD). Patients with ‘uncontrolled’ arterial hypertension – i.e. one of the thresholds mentioned above is exceeded – remain in the study. This holds as well for enrolled patients with any of the above-mentioned comorbid diagnoses, irrespective of their blood pressure values.

### Randomisation of the GP practices

As soon as the baseline assessment has been completed, GP practices will be randomised into intervention and control group. The randomisation will be performed by lot procedure. Thus, about half of the GPs will be assigned to the intervention and half of the GPs to the control group.

### Intervention

GPs of the intervention group will take part in an evaluated SDM training [6]. The training programme will be adapted to the requirements of hypertension treatment in general practice. The training involves at least two of three training sessions, with each session lasting three hours. The programme includes the following elements: (1) Information on arterial hypertension (epidemiology, treatment, patient adherence etc.), (2) principles of physician-patient-communication and risk communication, (3) information on the SDM concept including the implementation of the steps of the SDM process [7,10], (4) integration of Motivational Interviewing to enhance the patients’ intrinsic motivation to change health behaviour [8,9], (5) introduction of a decision table listing various options to lower cardiovascular risk, and (6) use of case vignettes for role plays simulating physician-patient consultations.

After the SDM training, GP practices will receive printed patient information developed by the German College of General Practitioners and Family Physicians (DEGAM) regarding blood pressure and the role of physical activity, healthy nutrition, and smoking cessation. GPs will be appealed to deliver patient information to the patients with hypertension.

GPs of the control group treat their patients as usual. They are invited to take part in the SDM training after the study.

### Data assessment and instruments

#### Clinical data

(1) Systolic and diastolic office blood pressure measurement in mmHg, (2) comorbidity: diabetes mellitus (and HbA1c), coronary heart disease / heart attack, ischaemic stroke / transient ischaemic attack or peripheral arterial occlusive disease, (3) cholesterol: total, HDL and LDL cholesterol, (4) 24 h ambulatory blood pressure monitoring (ABPM), (5) cardiovascular 10-year-risk score calculated according to the algorithm of the cardiovascular risk calculator *arriba* (http://www.arriba-hausarzt.de/arriba/index.html).

#### Patient self-reporting instruments

(1) Index reflecting patients’ intention to treat hypertension [12], (2) Medication Adherence Report Scale (MARS-D) [21], (3) helping relationship in taking medication [22], (4) Autonomy Preference Index (API) [23], (5) Trust in Physician Scale (TPS) [24], (6) knowledge about hypertension (8 items; developed by our research group), (7) medical decisions which are made with the GP during the consultation when ABPM results are reviewed, (8) patients’ perceived participation in medical decision making (SDM-Q-9) [25], (9) utilisation of further health care services.

#### Prescription data

(1) Current medication prescription plans of the GP practices (before each ABPM) including data on medication to lower blood pressure and cholesterol (ATC codes C02-C04 and C07–C10), dose and number of each entity, and time of day when a medication is taken. (2) Data of filled prescriptions (ATC codes C02-C04 and C07–C10). The prescription data will be used to define a medication possession ratio (MPR) [26] for each patient between the beginning of 2009 and the end of 2010. This feasibility subproject will be blinded for the study arm status of the patient.

All used scales – except knowledge questions and utilisation of further health care services – have been validated by other authors and translated into German by a consensus procedure. Retranslations (from German into English) were authorised by the original author. (The only exception is the Trust in Physician Scale because we could not get in contact with its authors.)

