### Study endpoints

Co-primary endpoints are (1) change of patients’ perceived participation (measured by SDM-Q-9) from T0 to T1, T2 and T3, evaluated by the mean effect over the three time points, and (2) change of systolic blood pressure (mean of 24 h), measured by ABPM [27], from T1 to T2 and T3, evaluated by the mean effect over the two follow-up time points. While the intervention may affect perceived participation directly at the first visit after intervention (T1), changes in blood pressure cannot be affected before the second visit (T2).

Secondary endpoints are (1) change of diastolic blood pressure (24 h mean), (2) change of knowledge score, (3) change of adherence, measured by MARS-D and the MPR, and (4) change of cardiovascular risk score (CVR), all evaluated by the mean effect over the two and three follow-up time points, respectively. While the intervention may affect knowledge directly after T0, the other secondary endpoints will be affected at T2 at the earliest.

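### The change-of-adherence endpoint needs MPR values before and after the intervention, but the article defines one MPR per patient over calendar 2009–2010

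*Protocol article*

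**What the plan says.** Three parts of the Protocol article bear on MPR.

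- **Prescription data.** Data on filled prescriptions will be used to "define a medication possession ratio (MPR) [26] for each patient between the beginning of 2009 and the end of 2010". The same paragraph adds: "This feasibility subproject will be blinded for the study arm status of the patient".
- **Study endpoints.** The third secondary endpoint is "change of adherence, measured by MARS-D and the MPR". The secondary endpoints are "all evaluated by the mean effect over the two and three follow-up time points, respectively". For everything except knowledge, "the other secondary endpoints will be affected at T2 at the earliest".
- **Analysis of primary and secondary endpoints.** Secondary endpoints are handled like the primary ones, in model (1). That model has an outcome for each patient at each follow-up time point k and a baseline value of the same measure as covariate. The endpoints named there as having T1 as baseline are systolic and diastolic blood pressure, MARS and cardiovascular risk. MPR is not among them.

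On timing, the ethics committee "approved this study on 26 February 2009" (Methods/Design). Under Recruitment procedure, "Recruiting takes place over half a year". Practices are randomised once baseline assessment is complete, and the training follows.

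**The concern.** A change needs at least two values of the same measure, and a mean effect over follow-up visits needs one value per visit. The definition of MPR gives one value per patient, computed over a calendar window that is not tied to T0, randomisation, training or any later visit. Taken literally, the endpoint cannot be formed.

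If the analyst compared the whole-window ratio between arms instead, dispensing from before the training would count as outcome. The training cannot have changed that dispensing, so those months add nothing to the contrast and pull it toward zero. This matters because MPR is the only adherence measure in the endpoint that is not self-reported, and adherence is one of the four research questions.

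**Working it through.** The article gives no figure for MPR to reproduce. The check sets the definitions side by side and then does calendar arithmetic.

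**Step 1: what the endpoint needs and what is supplied**

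| | Needed by Study endpoints and model (1) | Supplied under Prescription data |
|---|---|---|
| Baseline value | Yes (T1, or T0 in the sensitivity model) | None |
| Follow-up values | T2 and T3 | None |
| Time anchor | Study visits | Calendar, 2009–2010 |
| Values per patient | At least three | One |

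No section splits the window. This mismatch does not depend on when recruitment took place.

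**Step 2: how much of the window precedes the intervention**

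Time is counted in months from 1 January 2009, so the window runs from 0 to 24.

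- Approval on 26 February 2009: (31 + 25) / 30.4375 = 1.84 months.
- Earliest randomisation = start of recruitment + 6 months = 1.84 + 6 = 7.84, or late August 2009.
- Share before: 7.84 / 24 = 33%.
- Share after: (24 − 7.84) / 24 = 16.16 / 24 = 67%.

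The start of recruitment is not stated. The values below other than the first are assumed, to show the range.

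| Start (month) | Randomisation (month) | Months before | Months after | Share before |
|---|---|---|---|---|
| 1.8 (approval) | 7.8 | 7.8 | 16.2 | 33% |
| 6 | 12 | 12 | 12 | 50% |
| 12 | 18 | 18 | 6 | 75% |
| 18 | 24 | 24 | 0 | 100% |

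The window mixes the two periods for any start before mid-2010. With a later start it holds no post-intervention dispensing at all.

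**Step 3: whether the window reaches T3**

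This takes the earliest start and follow-up every 6 months. Counted from the end of recruitment, T1, T2 and T3 fall at 7.8 + 6 = 13.8, 19.8 and 25.8. T3 is then after the window closes. Counted from the first patient's baseline, T3 falls at 1.8 + 18 = 19.8, inside it. So T3 may lie outside the window, depending on patient and spacing.

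**Step 4: direction of the bias**

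Treat the whole-window MPR as roughly a time average. If the arms differ by d in each month after randomisation and by nothing before, the whole-window difference is about d × (share after). Under the earliest start this is 0.67d, and under a start at month 6 it is 0.50d. These are illustrations. The true factor depends on the unstated start date and on how quickly adherence responds.

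**The case against.** The strongest reply is that the dates may describe the span of dispensing data from which period-specific ratios are to be cut. The article does not use the word single, and listing MPR under a change endpoint suggests more than one value was intended. Dispensing from before recruitment would then be wanted, because a baseline MPR can come only from those months. An early start to the window is therefore not a defect in itself. This reading is possible, but the article does not state it: it speaks of a ratio for each patient over those dates, and no section links that ratio to visits. What stands is a conflict between stated rules rather than a detail left to the analysis plan.

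A second reply is that the MPR work is called a feasibility subproject, and that its comparison with MARS under Additional analyses needs no change score. Both are true, and they lower the stakes. But Study endpoints lists MPR without that qualification, so the two descriptions still need reconciling.

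A reader might also infer something stronger from the statement that adherence is affected from T2 at the earliest: that only months after T2 can carry an effect. With T0 between March and August 2009, that leaves 10 to 4 of 24 months (42% to 17%). The documents do not support this. The statement concerns when a measured endpoint can first show change, whereas MPR accumulates continuously and dispensing between T1 and T2 can already respond. Counting from T1 on the same assumed dates gives 16 to 10 months (67% to 42%).

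**Conclusion.** The point holds. As written, the MPR definition cannot deliver the change endpoint or enter model (1), and the sections must be reconciled. At least about 33% of the window precedes the intervention and at most about 67% follows it. These limits assume that no baseline assessment took place before approval, that recruitment took the stated half year, and that randomisation waited for it to finish. A later start raises the pre-intervention share.

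A contrast of the single ratio would be diluted toward zero, but the article does not allow the amount to be fixed. It would be tempting to conclude that MPR would look null even if the training worked. That does not follow: dilution shrinks an estimate without removing it, and the article gives no MPR effect size, standard deviation or power from which to judge.

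Severity is low to moderate. One component of one secondary endpoint is affected, and the bias is toward no effect. MARS-D is collected at baseline and at every follow-up, so it supports the change analysis without MPR. The co-primary analyses are untouched.

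**What to change.** Choose one of two courses, and fix it while the MPR work is still blind to arm.

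1. **Keep MPR in the endpoint.** From the same filled-prescription data, compute two ratios per patient: one for the period before the practice's randomisation or training date, and one from that date to T3 or the end of available data. Control practices have no training during the study, so the anchor must be a date that exists in both arms, such as randomisation. Analyse the post-period MPR with the pre-period MPR as covariate and a random practice effect. With one post-period value per patient, the visit-specific terms of model (1) drop out, and the text should say so.
2. **Treat MPR as feasibility work only.** Remove it from the change-of-adherence endpoint, leave MARS-D as the measure there, and keep the comparison of MPR with MARS under Additional analyses.

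The first course costs a re-cut of the filled-prescription data already planned and a few lines in the analysis plan. Its drawback is that shorter windows give noisier individual MPRs. A post-period starting at randomisation may also include some early months before adherence responds. The second course costs only a change of wording, but leaves the endpoint resting on self-report alone.

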#### Socio-demographic and other data

Besides age, gender, degree of education, employment status and family history of cardiovascular events we ask whether patients are living with a partner. Furthermore height and weight as well as tobacco consumption will be assessed.

### Study endpoints

Co-primary endpoints are (1) change of patients’ perceived participation (measured by SDM-Q-9) from T0 to T1, T2 and T3, evaluated by the mean effect over the three time points, and (2) change of systolic blood pressure (mean of 24 h), measured by ABPM [27], from T1 to T2 and T3, evaluated by the mean effect over the two follow-up time points. While the intervention may affect perceived participation directly at the first visit after intervention (T1), changes in blood pressure cannot be affected before the second visit (T2).

Secondary endpoints are (1) change of diastolic blood pressure (24 h mean), (2) change of knowledge score, (3) change of adherence, measured by MARS-D and the MPR, and (4) change of cardiovascular risk score (CVR), all evaluated by the mean effect over the two and three follow-up time points, respectively. While the intervention may affect knowledge directly after T0, the other secondary endpoints will be affected at T2 at the earliest.

#### Hypotheses on predictive factors

The study should also be used to investigate whether patient characteristics like API, CVR, MARS-D, Intention-To-Treat-Hypertension-Index, helping relationship in taking medication and high knowledge score may predict treatment effects.

### Study procedure

In all participating GP practices identical ABPM instruments will be installed by supervised personnel. Medical assistants (MAs) of GPs will be instructed about utilisation of the ABPM, recruitment procedure and data collection.

Patients who agree to take part in the study sign an informed consent form. Blood pressure, gender, age and comorbidity of patients who do not agree to take part in the study will be anonymously assessed to account for a possible selection bias due to the study enrolment.

#### Baseline assessment

The baseline assessment includes all clinical data, socio-demographic data and prescription data. Before the ABPM will be performed, patients complete a first questionnaire including socio-demographic data, intention-to-treat-hypertension index [12], medication adherence report scale (MARS-D) [21], helping relationship in taking medication [22], Autonomy Preference Index (API) [23], Trust in Physician Scale (TPS) [24], and knowledge about hypertension (8 items; developed by our research group).

If the average blood pressure in the ABPM protocol exceeds 130/80 mmHg (24 h mean) or 135/85 mmHg (daytime mean) or 120/70 mmHg (night mean), previous blood pressure treatment is considered as ‘uncontrolled’ [1,20,28]. These patients – as well as patients with any of the above-mentioned comorbidities – remain in the study. In the following visit GPs discuss with these patients possible consequences regarding the subsequent treatment. Immediately after this baseline consultation, patients will receive a second questionnaire including the above-mentioned self-reporting instruments ‘treatment decision made to control hypertension’ (instrument 7) and SDM-Q-9 (instrument 8).

